### 13.6.2 Leprosy Detection/Diagnosis

The utility of a medical diagnostic test is often expressed in terms of the receiver operating characteristic (ROC) for the test (37). The ROC is a plot of the relationship between the false positive rate (FPR), or 1-specificity, and the true positive rate (TPR), or sensitivity. Given a pair of individuals, one with and one without the medical condition of interest, the area under the ROC curve (AUC) is equal to the probability that the test will correctly discriminate between this pair. This study will be the first one using these test antigens in volunteers with the condition of interest making it difficult to establish a hypothesis concerning the AUC.

The study design provides for a variety of possible subset analyses for a given dose of each antigen. Nine combinations of volunteers expected to be non-reactive and reactive respectively are listed in the following table. This is not a definitive Phase III trial, although it has some characteristics in that specificity/sensitivity are considered in the analysis, thus adjustments for multiple comparisons are not considered here. The multiple comparison possibility will be considered at the time of actual data analysis.

Although the observational unit in this study is an individual injection site, the experimental unit is subject. Since subjects in C-1 will receive the higher dose of antigen and C-1b subjects the lower dose, results from C-1 and C-1b will not be combined to construct the ROC curve or to estimate the sensitivity/specificity of the antigens. However, independently, C-1 or C-1b will be used construct the ROC curve and estimate the sensitivity and specificity for each dose of the antigen separately. The estimates and sample sizes in the remainder of this section reflect this.

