## **6 RANDOMIZATION/ENROLLMENT/BLINDING PROCEDURES**

Upon successful completion of the screening procedures, the SC will assign each participant a unique subject number indicating enrollment. Each subject will be assigned to an antigen administration template derived from a randomization sequence provided by EMMES Corporation. This sequence randomly associates one of the templates to a study number, and is generated using a fixed blocked size to ensure template balance within each block. In order to preserve the randomization, the subject numbers must be assigned sequentially.

Should some of the subjects not return for the first or later readings, there is no plan to administer skin tests to additional subjects. The analyses presented in Section 13.6, "Sample Size Considerations", show that the study will be able to meet the primary statistical objectives, even should up to 10% of the subjects be lost to follow-up.

The person administering the antigens will be blinded as to their identity. Moreover, there is no recognized medical benefit of knowing the identity of an antigen in the event a subject must be treated for an adverse event. Therefore, unblinding will not occur during the study unless recommended by the SMC and approved by the DMID Project Officer (PO).

Adverse events, including serious adverse events, will not in and of themselves provide a cause for unblinding. The ISM may temporarily suspend enrolling further subjects pending discussion with the DMID PO and SMC. The Principal Investigator will report all SAEs to PPD Development Inc., DMIDs pharmacovigilance contractor, who will then forward the information to the DMID Study Coordinator for distribution to the DMID PO and the SMC to determine if the antigens should be unblinded, and if the study needs to be amended as a consequence of the SAE. In all cases of unblinding, the identity of antigens will only be made available to key study personnel and SMC members as necessary.

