### **9.3.3 Dosage of Investigational Product**

For Stage A and B, each individual will receive two injections of titrated doses of one of the two skin test antigens (in concentrations of 0.1 µg and 1.0 µg in 100 µl sterile diluent, 0.9% NaCl, approved for human use, Abbott Laboratories), one injection of 100 µl 5TU tuberculin/PPD Tubersol®; Aventis

Pasteur Inc., Swiftwater, PA, and one injection of 100µl diluent. For Stage C-1 and C-1b, each individual will receive each of the two skin test antigens at the high dose (1.0µg) only or low dose (0.1µg) only, respectively; and 2TU tuberculin/PPD, RT 23 SSI, Statens Serum Institute, Copenhagen, Denmark.

All injections will be in 0.1ml volumes from vials containing 0.5, 1.0 or 2.0 ml total. All injections will be made within 8 hours of the vials being opened. During this maximum 8 hour period cold storage (2-8°C) will be maintained. The concentration ranges to be tested are based on results of our Phase I study (see p. 12), previous skin testing in humans with Rees' antigen (optimum dosage is 1.0µg in 100µl), as well as our skin test results in guinea pigs.

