### 13.3 Study Design

This is a prospective study where the participants all receive the same set of antigens, but are randomized to receive them in different patterns, that is, according to different “templates”. The participants do not know which template is used and the readers, or evaluators are also blinded to the pattern of antigen delivery. Stages A and B randomized participants to only a single study antigen, at two doses for each volunteer, plus PPD and saline. Schemas for stages A plus B and C follow.

[figure not shown]

Volunteers in stage C-1 will receive both leprosy skin test antigens at the high dose of 1µg per 100µl and PPD at 2TU, while volunteers from stage C-1b will receive the same antigens at the low dose of 0.1µg per 100µl and PPD at 2TU. Since three test sites are required as compared to four in Stage A and B, they will be reassigned (2 sites on the first arm and one on the second arm), and administration templates will be randomized to different administration patterns. For Stage C-1 and C-1b, there will be 20 subjects from each study group, except healthy non-contacts (contacts of leprosy patients; BT/TT and BL/LL leprosy patients; and, tuberculosis patients).

[figure not shown]

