### Comparison Groups of Interest

#### ***Assuming Uniform Loss to Follow-up of 10% in each Group***

| Groups of Interest     | BT/TT Patients | Contacts of BL/LL Patients | Contacts of BL/LL Plus BT/TT Patients |
|------------------------|----------------|----------------------------|---------------------------------------|
| BL/LL Patients         | 36 and 36      | 36 and 36                  | 36 and 72                             |
| BL/LL Patients Plus TB | 72 and 36      | 72 and 36                  | 72 and 72                             |

Using a two tail-test with Type I error equal to 5% and Power equal to 80% the proposed analyses can detect a difference in area of 0.186 or less. This difference occurs for the worse case,  $AUC_0' = 0.5$  and the smallest sample size combination (BL/LL and BT/TT subjects,  $N=36$  and  $36$  respectively). Using the largest proposed sample ( $N=72$  and  $72$  for expected negative and positive responders, respectively) and a more optimistic null hypothesis of  $AUC_0' = 0.75$  results in a detectable difference of 0.101.

All of these analyses may be performed for both antigens, MLSA-LAM and MLCwA at both doses. Moreover, the ROC curves can be compared. The largest proposed sample size ( $N=72$  and  $72$  for expected negative and positive responders) is expected to be sufficient to detect a difference in the AUC in the range of 0.135 to 0.100.

This calculation is not setting a null hypothesis ( $AUC_0'$ ) for the basis of a successful study or designed to definitively test the difference in the two antigens. These values are provided however, to give an indication of the power inherent in the proposed sample size.

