ROC analyses involve both the expected positive and negative responding groups. Sensitivity and specificity analyses are restricted to each of these groups individually. The following table provides an indication of the precision obtainable in measuring sensitivity and specificity in this study, as determined by the half width of the confidence interval for some hypothetical results and appropriate sample sizes, as described above. Precision decreases as the observed proportion approaches 0.5 and as the sample size is decreased. Therefore, the worse case scenarios for sensitivity analyses would be restricting to BT/TT patients ( $N=36$ ) and observing a 50% sensitivity. In that case, the precision would be 0.16 or a confidence interval of (0.34, 0.66). At the other extreme, if all contacts of BL/LL plus BT/TT ( $N=72$ ) patients are included in the

analyses and a 0.95 sensitivity is observed, the precision is 0.05, or a confidence interval of (0.90, 1.00).

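### Section 13.6.2 bars pooling C-1 and C-1b, yet its ROC and sensitivity/specificity planning uses the pooled sizes 36 and 72; per dose they are 18 and 36

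*Protocol*

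**What the plan says.** Section 13.6.2 sets the rule: "results from C-1 and C-1b will not be combined to construct the ROC curve or to estimate the sensitivity/specificity of the antigens". Each part is to be used on its own, one dose at a time. The paragraph closes with an assurance: "The estimates and sample sizes in the remainder of this section reflect this".

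The design behind the rule is clear elsewhere. Section 13.3: "For Stage C-1 and C-1b, there will be 20 subjects from each study group, except healthy non-contacts". Section 9.3.3 says that in C-1 "each individual will receive each of the two skin test antigens at the high dose" only, and in C-1b at the low dose only.

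The comparison table in 13.6.2, headed "Assuming Uniform Loss to Follow-up of 10% in each Group", then lists 36 for each single group and 72 for each pair of groups. From those sizes the section states:

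- For the smallest comparison, 36 against 36 at a null AUC of 0.5, "the proposed analyses can detect a difference in area of 0.186 or less".
- For the largest, 72 against 72 at a null AUC of 0.75, the detectable difference is 0.101.
- For comparing two ROC curves at 72 and 72, the range is 0.135 to 0.100.
- For sensitivity in BT/TT patients alone, observed at 50%: "In that case, the precision would be 0.16 or a confidence interval of (0.34, 0.66").
- For contacts plus BT/TT patients (N=72), observed at 0.95, the half-width is 0.05.

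Section 6 relies on the section 13.6 calculations, saying they "show that the study will be able to meet the primary statistical objectives" even with 10% loss. Section 10.2.2 repeats the assurance.

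**The concern.** The no-pooling rule and the sample sizes cannot both hold. Only 20 BT/TT patients ever receive a given dose, so no per-dose analysis can contain 36 of them. The protocol's own safety calculation in 13.6.1 uses 18 per group for one part and reaches 36 only in the table that explicitly combines C-1 and C-1b.

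Section 3.1 makes estimation of sensitivity and specificity a primary objective, and 13.6.2 is the only place where the protocol justifies its size for that objective. Section 2.2 ties further studies to values in the region of 90% or above. A reader who trusts the table will believe the trial can judge that level more sharply than it can.

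**Working it through.** **Inputs.** 20 subjects per group in each part (sections 4.2 and 13.3); one dose per part (9.3.3); 10% loss, two-sided 5% error and 80% power (13.6.2).

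**Group sizes.**

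- One group, one dose: 20 × 0.9 = 18.
- Two groups, one dose: 40 × 0.9 = 36.
- The table's 36 for a single group is (20 + 20) × 0.9, i.e. both parts together. Its 72 is 80 × 0.9, i.e. two groups over both parts.

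**Half-widths.** Formula: 1.96 × √(p(1−p)/n).

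| n | p=0.5 | p=0.75 | p=0.9 | p=0.95 |
|---|---|---|---|---|
| 72 | 0.115 | 0.100 | 0.069 | 0.050 |
| 36 | 0.163 | 0.141 | 0.098 | 0.071 |
| 18 | 0.231 | 0.200 | 0.139 | 0.101 |

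The rows for 72 and 36 reproduce all eight entries of the protocol's precision table. At one dose:

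- BT/TT alone has n=18, so the worst case is 0.50 ± 0.23, or 0.27 to 0.73, instead of 0.34 to 0.66.
- Contacts plus BT/TT has n=36, so the best case at 0.95 is ± 0.07, or 0.88 to 1.00 after truncation, instead of ± 0.05.
- At 0.95 with n=18 the normal interval passes 1 (0.95 + 0.10 = 1.05). An observed 17/18 has an exact 95% interval of 0.73 to 1.00.

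**Detectable AUC difference.** Solve d = 1.96 × √V(A0) + 0.84 × √V(A0 + d), where, for m positives and n negatives, the Hanley-McNeil variance is V(A) = [A(1−A) + (m−1)(Q1−A²) + (n−1)(Q2−A²)]/(mn), with Q1 = A/(2−A) and Q2 = 2A²/(1+A).

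| Sizes | A0 | Computed | Protocol |
|---|---|---|---|
| 36 v 36 | 0.5 | 0.187 | 0.186 |
| 72 v 72 | 0.75 | 0.106 | 0.101 |
| 18 v 18 | 0.5 | 0.259 | (not given) |
| 36 v 36 | 0.75 | 0.146 | (not given) |

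The Obuchowski-McClish binormal variance taken at the null gives 0.1863 for the first row, matching 0.186. The 0.101 is reproduced only approximately. Scaling it directly gives 0.101 × √2 = 0.143, close to 0.146.

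**Comparison of two curves.** Halving both group sizes scales the stated range by about √2: 0.135 × 1.414 = 0.19 and 0.100 × 1.414 = 0.14. A direct calculation agrees if a within-subject correlation of 0.5 is assumed. At 72 and 72 it gives 0.134 (AUC 0.5) to 0.100 (AUC 0.8); at 36 and 36 it gives 0.190 to 0.141.

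**Against the 90% level.** If true sensitivity is 0.95, the chance of observing at least 90% is P(X ≥ 17 | n=18) = 0.77, against P(X ≥ 33 | n=36) = 0.90.

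**The case against.** Four points can be made for the plan.

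1. **Healthy non-contacts.** Stages A and B gave 50 subjects per antigen both doses, so about 45 after 10% loss, and sections 3.1 and 3.4 compare them with the Stage C groups. Adding them to BL/LL and TB patients gives 45 + 18 + 18 = 81 negatives per antigen and dose. At n=81 the half-widths are 0.109, 0.094, 0.065 and 0.047, slightly better than the stated n=72 row. This is a real possibility for specificity. It does not rescue the section. The rule in 13.6.2 refers to C-1 or C-1b alone, and the six cells shown contain no non-contacts (the text announces nine combinations, so a row may be missing). Nor can non-contacts raise the 18 or 36 available for sensitivity. Even with 81 negatives the detectable differences are about 0.21 (18 positives, AUC 0.5) and 0.135 (36 positives, AUC 0.75), still worse than stated.

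2. **The n=36 rows are correct arithmetic.** They are. Per dose, however, they describe two groups together, not BT/TT patients alone as the text labels them.

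3. **The figures are only indicative.** Section 13.6.2 disclaims any success criterion, 13.5 says no formal hypothesis is tested, and safety is the stated primary objective of C-1 and C-1b. This limits the consequence, but an indication that is wrong by a factor of about 1.4 still misinforms.

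4. **The 77% against 90% contrast is partly discreteness.** With 18 subjects, 16/18 is 88.9%. Counting it as in the order of 90% gives 94%, against 97% for 32/36 or more. The contrast should be read with that in mind; the interval widths are the firmer evidence.

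**Conclusion.** The concern holds. Section 13.6.2 forbids pooling the two parts, says its sizes respect that, and then uses sizes that only pooling can produce. Per dose, a single group has 18 evaluable subjects and two groups have 36. The worst-case half-width is 0.23 instead of 0.16 and the best case 0.07 instead of 0.05. The detectable AUC difference is about 0.26 instead of 0.186 for the smallest comparison and about 0.146 instead of 0.101 for the largest one tabulated. The two-curve range is about 0.19 to 0.14 instead of 0.135 to 0.100.

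The half-widths rest only on the protocol's own enrolment and loss figures. The AUC values depend on the variance formula: two-sided variants with null and alternative variance, or null variance alone, give 0.257 to 0.273 for 18 v 18, and variants with both variances give 0.143 to 0.156 for 36 v 36 at 0.75. The sample-size contradiction depends on none of these choices.

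**What to change.** Restate 13.6.2 per dose:

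- **Comparison table:** 18 for each single group and 36 for each pair of groups.
- **Precision table:** rows for n=18 (0.23, 0.20, 0.14, 0.10) and n=36 (0.16, 0.14, 0.10, 0.07), with the n=36 row labelled as two groups combined and the n=72 row removed. Correct the worked examples to ± 0.23 (0.27, 0.73) and ± 0.07.
- **AUC:** about 0.26 for 18 v 18 at 0.5, about 0.15 for 36 v 36 at 0.75, and about 0.19 to 0.14 for two curves, naming the variance formula and the correlation assumed.
- **Non-contacts:** if the Stage A/B subjects are meant to serve as negatives in these analyses, say so and add their sizes as a separate row.
- **Sections 6 and 10.2.2:** requalify the assurance about meeting the primary statistical objectives with 10% loss, so that for sensitivity and specificity it refers to the corrected precision.

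Exact or Wilson intervals would be sensible at these sizes but are optional. The cost is protocol wording only: no added subjects or procedures, and less favourable stated figures.

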### Comparison Groups of Interest

#### ***Assuming Uniform Loss to Follow-up of 10% in each Group***

| Groups of Interest     | BT/TT Patients | Contacts of BL/LL Patients | Contacts of BL/LL Plus BT/TT Patients |
|------------------------|----------------|----------------------------|---------------------------------------|
| BL/LL Patients         | 36 and 36      | 36 and 36                  | 36 and 72                             |
| BL/LL Patients Plus TB | 72 and 36      | 72 and 36                  | 72 and 72                             |

Using a two tail-test with Type I error equal to 5% and Power equal to 80% the proposed analyses can detect a difference in area of 0.186 or less. This difference occurs for the worse case,  $AUC_0' = 0.5$  and the smallest sample size combination (BL/LL and BT/TT subjects,  $N=36$  and  $36$  respectively). Using the largest proposed sample ( $N=72$  and  $72$  for expected negative and positive responders, respectively) and a more optimistic null hypothesis of  $AUC_0' = 0.75$  results in a detectable difference of 0.101.

All of these analyses may be performed for both antigens, MLSA-LAM and MLCwA at both doses. Moreover, the ROC curves can be compared. The largest proposed sample size ( $N=72$  and  $72$  for expected negative and positive responders) is expected to be sufficient to detect a difference in the AUC in the range of 0.135 to 0.100.

This calculation is not setting a null hypothesis ( $AUC_0'$ ) for the basis of a successful study or designed to definitively test the difference in the two antigens. These values are provided however, to give an indication of the power inherent in the proposed sample size.

ROC analyses involve both the expected positive and negative responding groups. Sensitivity and specificity analyses are restricted to each of these groups individually. The following table provides an indication of the precision obtainable in measuring sensitivity and specificity in this study, as determined by the half width of the confidence interval for some hypothetical results and appropriate sample sizes, as described above. Precision decreases as the observed proportion approaches 0.5 and as the sample size is decreased. Therefore, the worse case scenarios for sensitivity analyses would be restricting to BT/TT patients ( $N=36$ ) and observing a 50% sensitivity. In that case, the precision would be 0.16 or a confidence interval of (0.34, 0.66). At the other extreme, if all contacts of BL/LL plus BT/TT ( $N=72$ ) patients are included in the

analyses and a 0.95 sensitivity is observed, the precision is 0.05, or a confidence interval of (0.90, 1.00).

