### 13.9.3 Diagnostic Sensitivity/Specificity

These analyses will involve the selection of a cut-off for diagnostic testing, using the test antigens by dose, construction and comparison of ROC curves, and the determination of the sensitivity and specificity of the test antigens based on the selected cutoff points. This work will be based on the induration stimulated by the test antigens.

The text *Statistical Methods in Diagnostic Medicine* (37), will serve as a reference for most of the methods used in these analyses. An important assumption for many of these methods is that the distribution of the outcome measure (induration) follows an approximate binormal distribution, i.e. a combination of two normal distributions, one for the population with the condition of interest and another for the population without the condition. This assumption will be examined and exploited if it is met. Assuming that there is not a complete or virtually complete separation between the groups in their response, methods described by Schaefer, et.al. (38) will be examined to construct a cut-off for each of the antigens at each dose. For each cutoff the 95% confidence interval for the sensitivity and specificity based on this cutoff will be constructed. ROC curves will be constructed, the area under the curve and its 95% confidence interval computed and the antigens/doses will be compared to determine if there is a statistically significant difference in area.

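### The detectable AUC difference for comparing two ROC curves (0.135 to 0.100) states no correlation, baseline AUC or comparison; at the section's own reference AUCs the design does not deliver it for the between-subject dose comparison, nor for either comparison at the group sizes its no-pooling rule allows

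*Protocol*

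**What the plan says.** Section 13.6.2 of the protocol first treats a single ROC curve against a fixed value. At a two-sided 5% error rate and 80% power, for reference AUC 0.5 and 36 and 36, it says that "the proposed analyses can detect a difference in area of 0.186 or less". With reference AUC 0.75 and 72 and 72, this "results in a detectable difference of 0.101".

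It then notes that these analyses may be run for both antigens at both doses and that curves may be compared with each other. For that comparison it says that 72 and 72 "is expected to be sufficient to detect a difference in the AUC in the range of 0.135 to 0.100". No correlation, baseline AUC or named contrast accompanies the range. The closing paragraph calls the values indicative and refers to the two antigens.

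The analysis plan in 13.9.3 is wider: "the antigens/doses will be compared to determine if there is a statistically significant difference in area".

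On who receives what, 13.6.2 says "Since subjects in C-1 will receive the higher dose of antigen and C-1b subjects the lower dose", and for that reason bars combining the two parts for ROC curves. Section 13.3 gives both antigens to every Stage C subject, and section 5.3 excludes anyone who took part in an earlier stage.

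**The concern.** Two kinds of comparison sit behind one range. Antigen against antigen at one dose is paired, because each Stage C subject receives both. Dose against dose for one antigen is between different people, so the two AUC estimates are independent. The variance of a difference between AUCs depends heavily on that correlation, so a figure that suits one comparison need not suit the other.

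The protocol offers the figure as an indication of the power in the sample size, and it offers no other figure for comparing curves. Stage C-1b was added to study the lower dose and to supply a comparative low-dose population (Protocol Summary; section 13.2). A reader planning or interpreting the dose comparison would take 0.10 to 0.135 as detectable, and might give a non-significant result more weight than it can bear.

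**Working it through.** **Inputs.** Two-sided 5% and 80% power are stated for the one-curve calculation in 13.6.2 and are assumed to carry over. Group sizes are 72 and 72 as printed. Reference AUCs of 0.5 and 0.75 are the section's own one-curve anchors; using them for the two-curve range is an assumption. The correlation r between AUC estimates is not stated and is varied here. For dose against dose, r = 0 by design.

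**Variance of one AUC**, n per side:
- Hanley-McNeil: V(A) = [A(1−A) + (n−1)(Q1−A²) + (n−1)(Q2−A²)]/n², with Q1 = A/(2−A) and Q2 = 2A²/(1+A). For n = 72: V(0.5) = 0.00233 and V(0.75) = 0.00165.
- Binormal (Obuchowski), used as a second method: 0.00220 and 0.00187.

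**Plan's one-curve figures.** Solve d = 1.96·√V(A0) + 0.84·√V(A0+d).
- 36 and 36, A0 = 0.5: 0.186 to 0.187 by Hanley-McNeil (printed 0.186). This reproduces.
- 72 and 72, A0 = 0.75: 0.106 by Hanley-McNeil, 0.115 binormal (printed 0.101). This is close but not exact.

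**Two curves.** Solve d = 1.96·SE0 + 0.84·SE1, with SE0² = 2V(A0)(1−r) and SE1² = V(A0) + V(A0+d) − 2r·√[V(A0)V(A0+d)]. Results are Hanley-McNeil / binormal.

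| n per side | r | A0 = 0.5 | A0 = 0.75 |
|---|---|---|---|
| 72 | 0 | 0.189 / 0.185 | 0.153 / 0.164 |
| 72 | 0.3 | 0.159 / 0.155 | 0.130 / 0.139 |
| 72 | 0.5 | 0.134 / 0.131 | 0.111 / 0.118 |
| 72 | 0.6 | 0.120 / 0.117 | 0.099 / 0.106 |
| 36 | 0 | 0.26 / 0.26 | 0.212 / 0.224 |
| 36 | 0.5 | 0.190 / 0.185 | 0.156 / 0.165 |
| 36 | 0.6 | 0.170 / 0.166 | 0.140 / 0.149 |

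Example (72, r = 0, A0 = 0.5, Hanley-McNeil): SE0 = √(2 × 0.00233) = 0.0683 and SE1 = 0.0653, so d = 1.96 × 0.0683 + 0.84 × 0.0653 = 0.189.

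**Correlation needed for the printed range at 72 and 72:** 0.50 / 0.47 for 0.135 at AUC 0.5, and 0.60 / 0.65 for 0.100 at AUC 0.75.

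**Power at the printed differences, r = 0, 72 and 72.**
- 0.135 from 0.5: (0.135 − 1.96 × 0.0683)/√(0.00233 + 0.00213) = 0.02, which is 51%. Across both methods, and with the alternative variance used throughout, the range is 51% to 54%.
- 0.100 from 0.75: (0.100 − 1.96 × 0.0575)/√(0.00165 + 0.00106) = −0.24, which is 40%. Across the variants the range is 36% to 49%.
- A binormal simulation gave 53% and 49%.

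**Which N applies.** Each group has 20 subjects per part, or 18 after 10% loss. Two groups on each side of a curve give 36 and 36. The printed 72 and 72 is 4 × 18 per side, which needs C-1 and C-1b together, and 13.6.2 itself rules that out for ROC curves. At 36 and 36 with r = 0, power at the printed differences is 28% to 31% and 19% to 27%.

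**Sensitivity to baseline AUC.** With r = 0 and 72 and 72, the detectable difference is 0.138 / 0.151 at AUC 0.80 and 0.120 / 0.134 at 0.85. By Hanley-McNeil it is 0.097 at 0.90.

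**The case against.** A reader might infer that the protocol claims 0.135 to 0.100 for the dose comparison. It does not say so. The next paragraph speaks of the two antigens, which are paired within a dose, and the preparations share many proteins (section 9.1.1), so a correlation near 0.5 to 0.65 is not implausible. The authors may have had only that contrast in mind.

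A reader might also infer that the range is unattainable without correlation. That is too strong. No baseline AUC is given for it, and at about 0.8 to 0.9 independent curves reach at least its upper part. High AUCs are not foreign to the plan, since section 2.2 speaks of sensitivity and specificity around 90%.

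Nor can the range be called a miscalculation. The one-curve result at 72 and 72 and AUC 0.5 is 0.133 to 0.135 by Hanley-McNeil, close to the printed upper value, but this does not show how the range was obtained.

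Finally, section 13.5 disclaims formal hypotheses, the values are called indicative, and nothing in the document says that non-significance would be read as equivalence.

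These points limit the wording and the weight of the point. They do not supply the missing assumptions. Section 13.9.3 does plan a significance test across doses, the adjacent text covers both antigens at both doses, and no other figure is given. The antigen comparison does not reach the range either at 36 and 36, for AUC 0.5 to 0.75 and correlation up to about 0.6.

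**Conclusion.** The range is not usable as printed. It omits the correlation, the baseline AUC and the contrast, and for one of the two planned contrasts it is too favourable at the section's own reference AUCs. With 72 and 72 accepted, dose against dose detects about 0.19 at AUC 0.5 and 0.15 to 0.16 at AUC 0.75, with roughly 36% to 54% power at the printed values. Under the plan's own no-pooling rule, dose against dose detects about 0.26 and 0.21 to 0.22. Antigen against antigen, at correlation 0.5 to 0.6, detects about 0.17 to 0.19 and 0.14 to 0.165.

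This rests on carrying over two-sided 5% and 80% power, on reference AUCs of 0.5 and 0.75, and on the two variance formulas above. The zero correlation between doses is a design fact, not an assumption. Correcting N alone would not be enough, because the paired and independent comparisons would still share one figure.

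**What to change.** In 13.6.2, replace the range with two statements at the per-dose group sizes (at most 36 and 36 after 10% loss):

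1. Antigen against antigen within a dose, as a paired comparison. State the baseline AUC and the assumed correlation, and show the detectable difference for more than one correlation, for example 0.3 and 0.5.
2. 1.0 µg against 0.1 µg for the same antigen, as an independent-sample comparison with its own detectable difference and stated baseline AUC.

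In 13.9.3, add that antigens within a dose are compared by a paired AUC test (DeLong, for instance) and doses by an independent-sample test.

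The cost is two or three sentences and one recalculation, with no added subjects or procedures. The stated detectable differences become less favourable, most of all for the dose comparison.
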